## Abstract

**Background:**

Intensive care medicine continues to improve, with advances in technology and care provision leading to improved patient survival. However, this has not been matched by similar advances in ICU bedspace design. Environmental factors including excessive noise, suboptimal lighting, and lack of natural lights and views can adversely impact staff wellbeing and short- and long-term patient outcomes. The personal, social, and economic costs associated with this are potentially large. The ICU of the Future project was conceived to address these issues. This is a mixed-method project, aiming to improve the ICU bedspace environment and assess impact on patient outcomes. Two innovative and adaptive ICU bedspaces capable of being individualised to patients’ personal and changing needs were co-designed and implemented. The aim of this study is to evaluate the effect of an improved ICU bedspace environment on patient outcomes and operational impact.

**Methods:**

This is a prospective multi-component, mixed methods study including a randomised controlled trial. Over a 2-year study period, the two upgraded bedspaces will serve as intervention beds, while the remaining 25 bedspaces in the study ICU function as control beds. Study components encompass (1) an objective environmental assessment; (2) a qualitative investigation of the ICU environment and its impact from the perspective of patients, families, and staff; (3) sleep investigations; (4) circadian rhythm investigations; (5) delirium measurements; (6) assessment of medium-term patient outcomes; and (7) a health economic evaluation.

**Discussion:**

Despite growing evidence of the negative impact the ICU environment can have on patient recovery, this is an area of critical care medicine that is understudied and commonly not considered when ICUs are being designed. This study will provide new information on how an improved ICU environment impact holistic patient recovery and outcomes, potentially influencing ICU design worldwide.

**Trial registration:**

ACTRN12623000541606. Registered on May 22, 2023. 
https://www.anzctr.org.au/Trial/Registration/TrialReview.aspx?id=385845&isReview=true.

**Supplementary Information:**

The online version contains supplementary material available at 10.1186/s13063-024-08222-6.

## Background

Globally, intensive care units (ICUs) provide critical care and life support to 13–20 million acutely ill and injured patients every year [1]. Technological and clinical advances have contributed to increased survival of patients in recent years. These advances, however, have not been matched by advances in the design of ICUs. Despite longstanding recognition of the interrelationship between the environment and health, contemporary ICUs are increasingly medicalised, busy, and noisy environments that is suggested to hinder rather than promote recovery [2–4].

There is increasing evidence that the ICU bedspace environment, including excessive sound and alarms, artificial lighting, and lack of access to natural light and views, has negative effects on patients, their family members, and staff [5–9]. However, existing evidence is limited, and there is therefore inadequate, if any, evidence available to demonstrate causation or the ability to discern whether these negative outcomes are simply effects of critical illness and hospitalisation alone, as previous studies have not compared different or upgraded ICU bedspaces and impact on outcomes. These environmental and design factors contribute to the sleep deprivation and delirium commonly experienced by patients admitted to ICU, thereby potentially contributing towards increasing morbidity and mortality [10–17]. Environmental factors such as excessive sound or noise may adversely affect staff health and performance [18, 19]. The negative impact on staff wellbeing and mental health may therefore contribute to the high nursing turnover, reported to be as high as 36% annually, and thereby on current nursing shortages [18–22]. The cost of hospital employee turnover is estimated to be more than 5% of hospital budgets; replacing an experienced ICU nurse can cost up to USD $100,000 [22, 23].

The impact on patients may extend beyond admission, with disrupted sleep and delirium contributing towards the development of post-intensive care syndrome (PICS), a collection of complications including cognitive, physical, mental, and psychological disability, which affects up to 80% of patients discharged from critical care [24, 25]. The ongoing health problems and disability associated with PICS can severely impact the quality of life of patients and their families [26, 27]. Many ICU survivors never return to work and require significant caregiver support. This may detrimentally impact on their family members’ ability to work and their earning capacity, leaving them unable to provide for the family financially, with close to one third of patients reporting losing most or all family savings and their major source of income after serious illness [28]. Associated personal, social, and economic costs are immense.

To redress these issues, investment should be targeted towards solving these widely recognised design problems and evaluating the outcomes of environmental upgrades. Previous studies have suggested that a modified ICU environment is associated with a reduced delirium rate and ICU length of stay [29]. However, to date, there are limited studies directly investigating the relationship between ICU bedspace environmental upgrades and patient outcomes [30].

The ICU of the Future project is a mixed-method project, aiming to improve the ICU bedspace environment and assess impact on patient outcomes. This project commenced with modifiable environmental, technological, and design features contributing to suboptimal outcomes being identified via qualitative patient, family, and staff interviews [4, 31] and quantitative studies [32]. This was followed by a co-design process, used to redesign and develop an innovative and adaptive ICU bedspace capable of being individualised to patients’ personal and changing needs and aimed to optimise clinical efficiency, patient experience, and outcomes [33]. The new bedspace design has been implemented in the study ICU with patients admitted from January 2023. Table 1 summarises the main changes to the implemented bedspaces.

**Table 1 Tab1:** Main changes implemented for the upgraded bedspaces

Environmental factor addressed	What was implemented
Sound/noise reduction	
1. Improved sound absorption	1. Acoustically absorbent ceiling tiles and walls (satisfying infection control criteria) and softer floor vinyl
2. Improved sound blocking	2. Added doors to open-plan bedspaces with double layer of extra thick acoustic glass and optimal seals
3. Reduced sound production within bedspace	3. Repositioned alarms away from patients’ head, reconfigured and reduced alarm numbers, staff education
4. Improved sound control within bedspace	4. Introduced sound masking and beds with speakers built into them with the ability to link wirelessly to a patient entertainment system, enabling, e.g. individualised music therapy
Light	
1. Optimised lighting specific for two internal and windowless bedspaces	1. Installed a timed and programmed circadian lighting solution able to be modified to patients’ specific needs
Patient connectivity, stimulation, distraction, and engagement	
1. Improved patient stimulation and distraction	1. Patient entertainment system, materials, and colours were carefully chosen to make the space feel less clinical and overwhelming
2. Improved views and connectivity with nature in windowless bedspaces	2. Virtual window and artificial skylight with several available videos that can be selected based on personal preferences
3. Improved connectivity with family and friends	3. Virtual visiting
Staff solutions	
1. Support communication and workflow	1. Updated nurse call system installed, mobile solutions replaced static ones where able (e.g. workstation on wheels), decluttering the bedspaces where able

The aim of the study described in this protocol is to evaluate the impact of the ICU bedspace environmental upgrade on short- and medium-term patient outcomes and operational impact (health economic evaluation, objective environmental evaluation, and staff experience). Findings of the project will be relevant to a range of stakeholders, including health care administrators and providers, clinicians, patients, and their families.

## Design and methods

### Setting

This study will be conducted in a 27-bed adult ICU at a large urban Australian tertiary referral hospital specialising in cardiothoracic surgery and medicine. The ICU originally comprised 21 open-plan bedspaces and six isolation beds in three ‘pods’ of nine beds each, surrounding a central nursing station. Two of the windowless open-plan bedspaces were modified and will serve as the intervention beds; the remaining 25 will function as control beds. The unit admits approximately 1800 patients annually.

### Study design and plan

This is a prospective multi-component, mixed methods study including a randomised controlled trial (RCT) (Fig. 1). The study followed the SPIRIT reporting guidelines (Supplementary File) [34].

**Fig. 1 Fig1:**
[figure not shown]
Randomisation, recruitment, enrolment, and study plan

Study components encompass:

An objective environmental assessmentA description of the ICU environment from the perspective of patients, families, and staffSleep and circadian rhythm investigationsDelirium measurementsAssessment of medium-term patient outcomes 6 months after discharge from ICUA health economic evaluation

Data pertinent to each component will be collected and analysed using methods appropriate to type and source of data and analysed separately before being synthesised in a summative assessment.

#### RCT component

The primary study assessing patient outcomes (study components 3–6 described below) is an RCT, in which the two upgraded bedspaces are defined as intervention, while the 25 ‘conventional’ bedspaces serve as control. Eligibility screening, consent, and randomised allocation is a two-step process. All patients admitted to ICU are eligible to be randomised 1:1, except those deemed unsuitable for admission to the intervention bedspaces:

Patients requiring extracorporeal membrane oxygenation, intra-aortic balloon pump, or dialysisPatients admitted to ICU immediately following cardiac surgery, including transplantation

Patients will be randomly assigned to bedspaces as follows:

A random sequence of allocations to intervention and control bedspaces was established by the research coordinator and sealed in numbered, opaque envelopes. ICU floor coordinators and clinical personnel are blinded to this sequence until revealed at randomisation.Randomisation is completed by the ICU floor coordinator/admitting ICU doctor when:At least one intervention and one control bedspace are available at the time a patient is accepted for admission.The patient is eligible for randomisation (see above).The ICU floor coordinator or responsible clinician on duty opens the next envelope in sequence to reveal allocation of the patient to an intervention or control bedspace.The patient is assigned to the allocated bed.Patients will then be assessed for eligibility for participation in the study by a member of the research team (see ‘Recruitment’ section below).

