#### Case–control sub-study

Bedspaces in the study ICU differ regarding access to windows and natural light, potentially confounding outcomes. To investigate the effect of these variables, this study involves a concurrent observational case–control study utilising the three bedspaces that are most similar to the intervention bedspaces. These three internal and windowless bedspaces will function as ‘environmental control’ bedspaces. Thus, all patients admitted to these three bedspaces will also be invited to participate using the same protocols as the main RCT, but analysis will be adjusted to account for any potential bias in admission diagnosis, severity of illness, or other baseline data compared to the RCT cohort. Where patients are allocated to the environmental control bedspaces as part of the RCT, no further action will be taken, but patient data will also be utilised for the independent sub-analysis comparing intervention to environmental control bedspaces. Additionally, patients admitted to the intervention beds without being randomised will be approached for participation in the study as case control patients.

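### The on-duty staff who apply the entry conditions also open the allocation envelope, and no described step commits the patient before the reveal

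*Protocol article*

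**What the plan says.** All of this is in the protocol article.

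- **List and concealment (RCT component).** "A random sequence of allocations to intervention and control bedspaces was established by the research coordinator and sealed in numbered, opaque envelopes". Also: "ICU floor coordinators and clinical personnel are blinded to this sequence until revealed at randomisation".
- **Who randomises, and when (RCT component).** "Randomisation is completed by the ICU floor coordinator/admitting ICU doctor when" two conditions hold. The first is a bed condition: "At least one intervention and one control bedspace are available at the time a patient is accepted for admission". The second is that the patient is eligible: "All patients admitted to ICU are eligible to be randomised 1:1, except those deemed unsuitable for admission to the intervention bedspaces". Two groups are then listed as unsuitable, defined by organ support and by admission straight after cardiac surgery. The article does not name who makes that judgement.
- **Reveal and placement (RCT component).** "The ICU floor coordinator or responsible clinician on duty opens the next envelope in sequence to reveal allocation"; the sentence goes on to say that the allocation is that of the patient. Then: "The patient is assigned to the allocated bed".
- **Entry outside randomisation (Case–control sub-study).** "patients admitted to the intervention beds without being randomised will be approached for participation in the study as case control patients".
- **Screening and consent (RCT component, Recruitment).** A research team member does these after the bed has been assigned.

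**The concern.** Concealment has two parts. The person enrolling must not know the next allocation, and must not be able to withdraw or swap the patient once it is known. Sealed envelopes used in order serve the first part. The second needs a commitment recorded before the reveal, and the described procedure has none.

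This matters here because bedspace type is visible to everyone and one of the two entry conditions, bed availability, is an operational judgement. The unit has 27 beds, of which only two are intervention beds. If the opener sees an unwelcome result and then decides that a suitable bed was not really free, the patient becomes an ordinary unrandomised admission and the opened envelope is still at hand. Patient type could then become associated with arm at the point of allocation, before any selection through consent. The RCT is the article's primary study of patient outcomes, so its comparisons in sleep, circadian rhythm, delirium and six-month outcomes would all carry that imbalance.

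**Working it through.** The article gives no figure on this point, so there is none to reproduce. The check is of the sequence of steps, followed by an illustration of scale.

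**Sequence as written**

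1. The patient is accepted for admission.
2. At least one intervention and one control bed are free, and the patient is eligible. The floor coordinator or admitting doctor acts on these conditions.
3. The floor coordinator or responsible clinician opens the next envelope for that patient.
4. The patient goes to the allocated bed.
5. The research team screens and seeks consent.

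Steps 2 and 3 fall to overlapping on-duty roles. That they also judge suitability is a close inference, since no one else is named. Between steps 2 and 3 the article describes no log entry, no identifier written on the envelope and no independent check. Numbering fixes the order of the envelopes but not which patient receives each one. Because the sub-study accepts unrandomised patients in the intervention beds, a diverted patient would not stand out. The counts that the article promises (Data collection and monitoring; Component 6) cover patients approached, consented, lost or dead. They do not cover eligible admissions that bypassed randomisation.

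**Illustration of scale**

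*From the article:* about 100 patients recruited (Recruitment, estimate of numbers), randomised 1:1, hence about 50 per arm. Delirium is assessed in enrolled patients (Component 5), so 50 per arm is the relevant size.

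*Assumed:* two equal prognostic halves with delirium risks of 20% and 50%, no true effect, and a fraction f of allocations steered in one direction with perfect sorting.

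*Formulas:*
- Lower-risk arm: p₁ = 0.20(0.5 + f/2) + 0.50(0.5 − f/2) = 0.35 − 0.15f
- Higher-risk arm: p₂ = 0.35 + 0.15f
- Spurious difference: d = p₂ − p₁ = 0.30f
- SE = √{[p₁(1 − p₁) + p₂(1 − p₂)]/50}
- Rejection probability = 1 − Φ(1.96 − d/SE) + Φ(−1.96 − d/SE)

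| f | p₁ | p₂ | d | SE | d/SE | Two-sided error |
|---|---|---|---|---|---|---|
| 10% | 0.335 | 0.365 | 0.03 | 0.0953 | 0.31 | 6.1% |
| 20% | 0.320 | 0.380 | 0.06 | 0.0952 | 0.63 | 9.7% |
| 30% | 0.305 | 0.395 | 0.09 | 0.0950 | 0.95 | 15.8% |

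The documents give no amount of steering and no such risks, so the table shows only how the bias would scale if steering occurred.

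**The case against.** The strongest case against has five parts.

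- **The written order already ties the envelope to a patient.** Acceptance and eligibility come first, and the envelope reveals that patient's allocation. Opening first and matching later would breach the procedure. This stands: the plan does not permit a swap. It also does not describe anything that would prevent or reveal one.
- **The safeguards are real.** Sealed, numbered, opaque envelopes used in order, with clinical staff blind to the list, are an accepted method. This stands. A reader might infer that staff can learn the next allocation in advance. The documents do not support that: it would need tampering, a leak or a predictable scheme, and none is described.
- **The suitability exclusions are mostly factual.** This stands, and leaves bed availability as the condition with room for discretion.
- **Unrandomised use of the intervention beds has an innocent cause.** Whenever no control bed is free, the bed condition fails. Such patients go to the sub-study and not to the randomised comparison. This stands: that route is not evidence of steering, only a place where a diverted patient would look normal.
- **The article is condensed.** Envelope custody and logging may be in the full protocol. This lowers the weight of the point. It does not change the stated assignment of roles.

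A reader might also make much of the research coordinator, who made the list and is not named among those kept blind. That is secondary. The coordinator is not described as opening envelopes or placing patients, and research staff recruit only once the bedspace is visible. Knowledge of the list would matter only if it reached the clinical staff.

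**Conclusion.** The point holds as a weakness in an otherwise reasonable method. The same on-duty roles control entry, reveal and placement, and the described steps contain no commitment before the reveal, so an allocation could be reconsidered after it is seen. The documents do not show that this happens, that staff prefer particular patients for the upgraded beds, or that future allocations are predictable.

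The size cannot be estimated from the documents. The error rates of about 6, 10 and 16% rest wholly on the assumed risks, the assumed share steered and one-directional sorting. A calculation on the roughly 250 randomised would give larger error rates, but it would not apply, because delirium is measured only in enrolled patients. This is a cheap improvement worth making, not a flaw that invalidates the design.

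**What to change.** Release each allocation only after the patient ID, time, eligibility and the free intervention and control beds have been recorded. Either of two routes would do:

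- a concealed electronic form, in the study's existing electronic database if that offers one; or
- if envelopes stay, writing these items on the sealed envelope before it is opened.

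In addition:

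- reconcile envelope numbers with the admission log at regular intervals, for example monthly;
- log every eligible admission placed without randomisation, with the reason;
- state that the list is made and held by someone outside recruitment.

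The cost is a small set-up task and about a minute of entry per admission, with no extra patients or staff. The downside is that short delay at bed assignment. The change can be introduced while the trial is running.

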#### Case–control sub-study

Bedspaces in the study ICU differ regarding access to windows and natural light, potentially confounding outcomes. To investigate the effect of these variables, this study involves a concurrent observational case–control study utilising the three bedspaces that are most similar to the intervention bedspaces. These three internal and windowless bedspaces will function as ‘environmental control’ bedspaces. Thus, all patients admitted to these three bedspaces will also be invited to participate using the same protocols as the main RCT, but analysis will be adjusted to account for any potential bias in admission diagnosis, severity of illness, or other baseline data compared to the RCT cohort. Where patients are allocated to the environmental control bedspaces as part of the RCT, no further action will be taken, but patient data will also be utilised for the independent sub-analysis comparing intervention to environmental control bedspaces. Additionally, patients admitted to the intervention beds without being randomised will be approached for participation in the study as case control patients.

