### Recruitment

For an estimated study period of 2 years, all patients randomised to an intervention or control ICU bedspace as part of the RCT or admitted to environmental control bedspaces as part of the case–control study will be screened for suitability to participate in the research study. Suitable patients will be approached by a member of the research team as soon as possible after admission to ICU, in consultation with the treating clinical team. As patient status commonly changes throughout ICU admission, patients may be screened daily until discharge and may be recruited to the study at any time during their admission to ICU if suitable based on the following inclusion/exclusion criteria:

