**Fig. 2 Fig2:**
[figure not shown]
Study schedule of enrolment, intervention, and assessments

Patients for whom consent is obtained will complete the study components listed below. Based on annual admission numbers and current admission diagnoses and presentations, the average number of patients eligible for randomisation per bedspace in the study facility is approximately 30 per year. We therefore estimate that approximately 250 patients will be randomised over 2 years. We expect that approximately 50 patients will be ineligible for participation for various reasons and based on other studies in the unit we have conservatively estimated a 50% patient decline rate. We therefore estimate that approximately 100 patients will provide consent and be recruited to this study over the 2-year study period.

A power calculation for this study is not possible, due to the lack of studies reporting the impact of environmental upgrades on patient outcomes. Therefore, an interim analysis will be conducted after 6 months of data collection, focussing on recruitment rate, completion rate for the various study components, and in-hospital outcome measures, with a power calculation performed based on this data to determine the number of participants required.

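### The environmental-control sub-study does not limit its controls to patients who could have been randomised, so a subset has no counterpart in the intervention beds and the stated general adjustment may leave bias

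*Protocol article*

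**What the plan says.** The RCT component section defines who may be randomised: "All patients admitted to ICU are eligible to be randomised 1:1, except those deemed unsuitable for admission to the intervention bedspaces". Two groups are then listed as unsuitable: patients needing ECMO, a balloon pump or dialysis, and patients arriving straight from cardiac surgery or transplantation.

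The Case–control sub-study section addresses confounding by windows and natural light through three internal, windowless beds. Of these it says that "all patients admitted to these three bedspaces will also be invited to participate using the same protocols as the main RCT". For differences in case mix it relies on adjustment: "analysis will be adjusted to account for any potential bias in admission diagnosis, severity of illness, or other baseline data compared to the RCT cohort". Randomised patients who happen to be allocated to these beds count as well: "patient data will also be utilised for the independent sub-analysis comparing intervention to environmental control bedspaces". On the intervention side, "patients admitted to the intervention beds without being randomised will be approached for participation in the study as case control patients".

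The Recruitment section gives two routes into screening. One is randomisation. The other is for patients "admitted to environmental control bedspaces as part of the case–control study will be screened for suitability to participate in the research study". The inclusion and exclusion criteria that follow apply to both routes. They cover residence, English, expected stay, consent, age, imminent death, sedation, neurological insult and behaviour. They do not mention ECMO, balloon pump, dialysis or recent cardiac surgery.

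**The concern.** The bar on certain patient types belongs to randomisation, and the sub-study's control route does not pass through randomisation. Read as written, the text lets barred types into the control side while the design keeps them out of the intervention side. The effect of the upgraded bed in those patients cannot be estimated from data; a model can only extrapolate to them.

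This sub-study is the plan's means of separating the bed upgrade from access to windows and daylight. If part of its control group consists of post-surgical or organ-support patients with no intervention-bed equivalent, a difference in sleep, delirium or length of stay could reflect who was in the beds and not the beds themselves. The limitations in the Discussion cover imperfectly matched beds, not mismatched patients.

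**Working it through.** **1. The plan's own figure.** No recruitment figure is given for the sub-study. The RCT estimate in the Recruitment section reproduces: (250 randomised − 50 ineligible) × 0.5 = 100 recruited. The 250 is close to 30 per bed-year × 2 beds × 2 years × 2 arms = 240, which is consistent with an approximate figure.

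**2. How large could the non-overlapping group be?** Inputs: "The unit admits approximately 1800 patients annually" over 27 beds (Setting), and "the average number of patients eligible for randomisation per bedspace in the study facility is approximately 30 per year" (Recruitment).

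- Admissions per bed-year: 1800 / 27 = 66.7
- Share eligible for randomisation: 30 / 66.7 = 45%
- Share not eligible: 1 − 0.45 = 55% (62.5% if 25 are eligible, 47.5% if 35)
- Three beds over 2 years: 3 × 2 × 66.7 = 400 admissions, of which 3 × 2 × 30 = 180 are eligible and 400 − 180 = 220 are not

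These are admissions at the unit average, before screening and consent.

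**3. Does adjustment deal with it?** A simulation with a true effect of zero, 60 intervention and 90 control patients, and 1000 runs per setting. The assumptions are illustrative and not from the protocol: barred types occur only among controls; they are 0.5 SD more severe; severity has a coefficient of 0.3; and they have a further outcome deficit D of 0.3 or 0.5 SD that severity does not capture. Entries are the mean estimated effect (intervention minus control, in residual SD units) for D = 0.3 / 0.5.

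| Barred share of controls | Unadjusted | Severity only | Severity + barred-type indicator | Restricted to eligible |
|---|---|---|---|---|
| 10% | −0.049 / −0.068 | −0.031 / −0.053 | −0.001 / −0.001 | −0.001 / −0.001 |
| 30% | −0.141 / −0.195 | −0.096 / −0.142 | −0.008 / 0.001 | −0.008 / 0.001 |
| 55% | −0.255 / −0.353 | −0.165 / −0.263 | −0.011 / 0.004 | −0.011 / 0.004 |

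The unadjusted column agrees with the formula −share × (0.3 × 0.5 + D). At 55% this gives −0.55 × 0.45 = −0.248 and −0.55 × 0.65 = −0.358.

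Severity alone leaves a spurious effect that favours the intervention if barred patients do worse. An explicit indicator and restriction both bring it to about zero. At the 55% share the standard error rises from about 0.16–0.17 to about 0.20.

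**4. Is bed type nearly inseparable from barred status?** With 60 versus 90 patients and a barred share of 0 versus 55%, the intervention fraction is 0.4 and the overall barred fraction is 0.6 × 0.55 = 0.33. The covariance is −0.4 × 0.33 = −0.132. The correlation is −0.132 / √(0.24 × 0.2211) = −0.57, and the variance inflation is 1 / (1 − 0.57²) ≈ 1.5. That is moderate collinearity, well short of aliasing.

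**The case against.** The strongest reply is that the plan already answers the point. Using the RCT's protocols could be read as carrying over the randomisation criteria, and the promised adjustment names admission diagnosis as well as severity. A diagnosis term may well pick up post-cardiac-surgery patients, and treatment details recorded on the case report forms could identify the rest. The full protocol may also define the analysis population more closely.

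Part of this stands. The severity-only column above is not the stated plan; it shows what happens when adjustment misses the barred types. But the reading that the bar carries over is not secure. The same sentence invites all patients in these beds and then expects a case mix different from the RCT cohort, which points the other way. A diagnosis term need not capture ECMO, balloon pump or dialysis.

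The later screening does not close the gap either. Patients may be re-screened daily and recruited at any time in the ICU stay, so a sedation exclusion may only delay entry. The 24-hour rule after a general anaesthetic governs the start of sleep measurement, not enrolment.

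A reader might go further and infer that adjustment cannot repair the comparison, or that bed type is almost aliased with surgical or organ-support status. The documents support neither. An indicator for the barred types works as well as restriction, and about 45% of average admissions are eligible for randomisation, so there is real overlap. Randomised patients allocated to these beds meet the criteria by definition.

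**Conclusion.** The point holds as a moderate issue in a secondary observational comparison. As written, the sub-study admits to its control side patient types that the design keeps out of the intervention beds, and the general adjustment it describes does not reliably remove the resulting bias.

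The 55% is an upper guide to the barred share. It assumes admissions are spread evenly over 27 beds, although the case mix of the three beds is not given. It counts everyone not eligible for randomisation, and the protocol's use of eligible may reflect other factors such as bed availability. It also precedes the participation criteria and consent. A reader might take 220 of 400 as the number of analysed controls without a counterpart; that number cannot be derived from the document. The unit's cardiothoracic specialty does make a trivial share unlikely. The size and direction of any bias depend on the illustrative assumptions in the simulation.

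Nor should the point be read as touching the trial's main result: both randomised arms pass through the same criteria.

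**What to change.** Add one sentence to the Case–control sub-study section: the comparison of intervention with environmental-control beds includes only patients who met the RCT's randomisation criteria at ICU admission. Alternatively, state that following the RCT's protocols includes those criteria. Adjust for diagnosis and severity within that population, and report the other enrolled patients descriptively.

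Apply the same rule to non-randomised intervention-bed patients. It should remove few or none of them, but it makes the two sides symmetric. Settle the rule before outcomes are compared, so that the population is not chosen after the fact. Enrolment need not change, since the restriction can be applied at analysis if the criteria at admission are recorded.

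The cost is fewer sub-study controls: about 3 × 2 × 30 = 180 eligible admissions over 2 years at the unit average, before screening and consent, in place of about 400. Little is lost for the bed contrast, because under a model that identifies the barred types those controls contribute almost nothing to it.
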